### **[To be completed once every year by patient]**

- ☐ Asthma control questionnaire (ACQ)  
Mean score \_\_\_\_\_

- ☐ Asthma Quality of Life Questionnaire (AQLQ)  
Mean score \_\_\_\_\_
- ☐ Work productivity and Activity Impairment (WPAI)  
Mean score \_\_\_\_\_
- ☐ Health care utilization Questionnaire  
Mean score \_\_\_\_\_
- ☐ Checklist Individual Strength  
Mean score \_\_\_\_\_
- ☐ Severe asthma Questionnaire  
Mean score \_\_\_\_\_

**[To be completed once every year by case-manager]**

Is patient lost to follow-up?

- ☐ yes
  - ☐ Patient passed away
  - ☐ Patient changed email address
  - ☐ Patient withdrew consent
  - ☐ Other \_\_\_\_\_
- ☐ No

Date of examination (dd-mm-yyyy):

Height: \_\_\_\_\_ cm  
 Weight: \_\_\_\_\_ Kg  
 BMI: \_\_\_\_\_ Kg/m^2

Smoking Status:

- ☐ Never Smoker[SEP]
  - ☐ Ex-Smoker (Quit smoking >12 months)
  - ☐ Current Smoker
- Current number of Pack years: \_\_\_\_\_

Has patient ever been admitted to ICU for asthma?

- ☐ Yes
- ☐ No

If yes, total number of ICU admissions:  
Has patient ever been intubated due to asthma?

- ☐ Yes
- ☐ No

If yes, total number of intubations:

Has the patient ever attended rehabilitation

- ☐ Yes
  - How often? \_\_\_\_\_ times
  - Last time \_\_\_\_\_ years ago
- ☐ No[SEP]
- ☐ Unknown

Has the patient ever undergone bronchial thermoplasty?

- ☐ Yes  
Date/year \_\_\_\_\_
- ☐ No[SEP]
- ☐ Unknown

Has spirometry ever been performed (If done multiple times, please report most current result)[SEP]

- ☐ Yes
- ☐ No

If Yes, when was most recent pulmonary function test performed? (dd/mm/yyyy)

If Yes, which values are available?

- ☐ Pre-bronchodilator values
- ☐ Post-bronchodilator values

|          | PRE
BRONCHODILATOR |                | POST
BRONCHODILATOR |                |
|----------|-----------------------|----------------|------------------------|----------------|
| FEV1     | L                     | %
predicted | L                      | %
predicted |
| FVC      | L                     | %
predicted | L                      | %
predicted |
| FEV1/FVC | %                     |                | %                      |                |

Has exhaled NO testing ever been performed?

- ☐ Yes
- ☐ No

If yes, please report date of most recent result:

FeNO \_\_\_\_\_ppb

Has CO diffusion capacity been performed (ever)?

- ☐ Yes
- ☐ No

If yes, please report date of most recent result:

DLCO: \_\_\_\_\_ mmol/min/kPa and \_\_\_\_\_ % predicted

Has bodyplethysmography (body box) ever been performed?

- ☐ Yes
- ☐ No

If yes, please report date of most recent result:

TLC: \_\_\_\_\_ L and \_\_\_\_\_ % predicted

RV: \_\_\_\_\_ L and \_\_\_\_\_ % predicted

Has bronchial provocation testing with methacholine ever been performed ?

- ☐ Yes
- ☐ No

If yes, please report date of most recent result:

- ☐ Positive (BHR demonstrated, FEV1 decline  $\geq 20\%$ )
- ☐ Negative (BHR not demonstrated, FEV1 decline  $< 20\%$ )

Has blood cell differential counting been performed in the last 5 years?

- ☐ Yes
- ☐ No

If yes, please report date of most recent result:

- Leukocytes: \_\_\_\_ x 10E9 and \_\_\_\_ %
- Neutrophils: \_\_\_\_ x 10E9 and \_\_\_\_ %
- Eosinophils: \_\_\_\_ x 10E9 and \_\_\_\_ %

If yes, what was the highest eosinophil count ever measured?

Has blood glucose or HbA1c been measured during the last year?

- ☐ Yes
- ☐ No

If yes, please report date of most recent result:

Fasting glucose level:

Hba1c level

Has Blood Gas Analysis been performed/

- ☐ Yes
- ☐ No

If yes, please report date of most recent result:

pH \_\_\_\_\_ pCO2: \_\_\_\_\_ kPa / \_\_\_\_\_ mmHg; pO2: \_\_\_\_\_ kPa /  
\_\_\_\_\_ mmHg;

Has total serum IgE testing been performed?

- ☐ Yes
- ☐ No

If yes, please report date of most recent result:

\_\_\_\_\_ IU/ml or kU/l

Has a routine allergy test RAST/CAP or skin prick testing even been performed?

- ☐ Yes, positive
- ☐ Yes, negative
- ☐ No

If yes, please report date of most recent result:

Has allergy to aspergillus ever been tested?

- ☐ Yes, positive
- ☐ Yes, negative
- ☐ No

If yes, please report date of most recent result:

Has allergy to food ever been tested?

- ☐ Yes, positive
- ☐ Yes, negative
- ☐ No

If yes, please report date of most recent result:

Has sputum analysis (cell counts) ever been performed?

- ☐ Yes
- ☐ Yes, but inadequate sample
- ☐ No

If yes, please report date of most recent result:

\_\_\_\_\_ % Eosinophils  
\_\_\_\_\_ % Neutrophils

Has sputum culture been performed during last year?

- ☐ Yes, positive for pathogens
- ☐ Yes, negative for pathogens
- ☐ Yes, throat bacteria
- ☐ No

If yes, please report date of most recent result:

Has Chest X-Ray ever been performed?

- ☐ Yes, findings compatible with asthma[LSEP]
- ☐ Yes, findings compatible with other pulmonary disorders
- ☐ Yes, normal findings
- ☐ No

If yes, please report date of most recent result:

Has Chest HRCT ever been performed

- ☐ Yes

☐ No

If yes, please report date of most recent result:

- ☐ Bronchiectasis[L]  
[SEP]
- ☐ Emphysema
- ☐ Tree-in-bud configurations
- ☐ Other pulmonary abnormalities
- ☐ No abnormal findings

Has DEXA-scan ever been performed

- ☐ Yes, pathological findings
- ☐ Yes, normal findings
- ☐ No

If yes, please report date of most recent result:

Has bronchoscopy ever been performed

- ☐ Yes, findings compatible with asthma[L]  
[SEP]
- ☐ Yes, findings compatible with other lung diseases
- ☐ Yes, normal findings
- ☐ No

If yes, please report date of most recent result:

Does the patient have one of the following co-morbidities

Atopic dermatitis

- ☐ Yes
- ☐ No or very unlikely[L]  
[SEP]
- ☐ Only in the past
- ☐ Unknown

Allergic rhinoconjunctivitis

- ☐ Yes
- ☐ No or very unlikely[L]  
[SEP]
- ☐ Only in the past
- ☐ Unknown

[L]  
[SEP]

Chronic rhinosinusitis

- ☐ Yes
- ☐ No or very unlikely[L][SEP]
- ☐ Only in the past
- ☐ Unknown

[L][SEP]

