### *Data Collection Schedule*

All data points collected for the registry will be collected as part of the asthma clinic. Investigators will be asked to evaluate participants at least once a year. The study calls for the documentation of annual assessments, with predefined range of tolerance of  $\pm 1$  month.

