## Forms and data handling

A complete CRF is attached in the Appendix. The data are entered electronically via internet-based technology. The SHARP CENTRAL Registry web-portal is separated into several parts with different access rules. Any given site investigator in SHARP CENTRAL Registry is allowed to see only data on study participants under the care of the study site to which the site investigator is affiliated. SHARP CRC is allowed to view all data of all centres for plausibility checks, quality control and monitoring. The whole database is saved on a server.

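### The yearly smoking item has no box for a quit of 12 months or less and no quit date, so most patients who stop smoking between visits fit no category at the next one

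*Protocol*

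**What the plan says.** Appendix 1 of the Protocol contains the case report form. The section Forms and data handling describes it thus: "A complete CRF is attached in the Appendix". The form is therefore the intended instrument and not an extract.

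The part of the form headed "To be completed once every year by case-manager" asks for smoking status. The choices are never smoker, "Ex-Smoker (Quit smoking >12 months" and "Current Smoker". The only other smoking field is "Current number of Pack years". The item has no definition of a current smoker, no date of quitting and no option for unknown.

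On timing, Data Collection Schedule states: "The study calls for the documentation of annual assessments", "with predefined range of tolerance of" plus or minus 1 month. The Study design paragraph of the overview says that follow-up visits collect the same data as baseline. No other part of the Protocol says how to code a patient who stopped smoking within the last year.

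**The concern.** The categories of a status item should cover every patient. Here, a patient who stopped 6 or 11 months ago is not a never smoker, does not meet the printed ex-smoker rule, and is a current smoker only if that undefined box is read as taking everyone left over. The person completing the form has three courses: tick current, tick ex-smoker against the rule, or leave the item blank. The form does not say which to choose.

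The 12-month cut-off also equals the visit interval. The gap therefore catches most patients who stop smoking during follow-up at the first visit where this could be recorded.

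The Protocol's objectives cover phenotype and response to treatment at baseline and during follow-up, and it plans longitudinal analyses and a search for predictors of response. Smoking is a plausible confounder of change in the lung function, exhaled nitric oxide and symptom scores collected on the same form. If sites resolve the gap differently, the difference enters the merged data as an apparent difference between sites or countries. Comparing entries with source records cannot settle which box is right when no rule exists.

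**Working it through.** The Protocol gives no figure to reproduce for this item, so the check is interval arithmetic.

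**Inputs**

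- Ex-smoker cut-off: more than 12 months (Appendix 1, smoking status).
- Nominal visit interval: 12 months, tolerance plus or minus 1 month (Data Collection Schedule).
- Permitted intervals: 11 to 13 months if the earlier visit is the fixed anchor (baseline); 10 to 14 months if both visits may drift.
- Missed visits: kept as missing data without withdrawing the patient (Investigator Withdrawal of Subjects), so the next attended visit may come about 24 months after the last.
- Assumption, not in the Protocol: the quit time is uniform between the two visits and the patient stays quit.

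**Formula.** Let L be the months between two attended visits. A patient who smoked at the first and then stopped has been quit for less than L months at the second. The ex-smoker box fits only if that time exceeds 12 months, which has probability max(0, L − 12)/L. The share without a matching box is 1 minus this.

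| L (months) | Ex-smoker box fits | No matching box |
|---|---|---|
| 10, 11 or 12 | 0 | 100% |
| 13 | 1/13 = 7.7% | 92.3% |
| 14 | 2/14 = 14.3% | 85.7% |
| 24 (one visit missed) | 12/24 = 50% | 50% |
| 26 (one visit missed, both windows used) | 14/26 = 53.8% | 46.2% |

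**Average over the window.** Let each drifting visit fall uniformly within 1 month of its due date.

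- First interval (baseline fixed): L − 12 is uniform on (−1, 1), so the mean of max(0, L − 12) is 1/4. Then 0.25/12 = 2.1% fit the box and 97.9% do not.
- Later intervals (both visits drift): L − 12 is the difference of two such uniforms, and the mean of max(0, L − 12) is 1/3. Then 0.333/12 = 2.8% fit and 97.2% do not.
- Averaging the ratio (L − 12)/L per interval, instead of weighting by interval length, gives 98.0% and 97.4% by simulation.

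**Duration of the gap.** For a patient who stays quit and attends on schedule, about 3% are still at 12 months or less at the second visit after quitting. The problem therefore usually affects one annual record.

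**Baseline.** A patient who quit in the 12 months before the baseline visit has no matching box, whatever the follow-up interval.

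**The case against.** The strongest reply is that current smoker can be read as everyone who does not meet the ex-smoker rule. If all sites did this, the status would lag but not be lost. The form records the date of examination each year. Suppose the last current record is dated D1 and the first ex-smoker record D2. The quit then lies between D1 minus 12 months and D2 minus 12 months, a window of about one year, which is the same resolution as a yearly item with no cut-off. This stands where sites code consistently and the patient stays quit and attends. It fails for relapse, missed visits, a patient's last record and mixed coding, and the form does not state the convention it needs.

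The 97% is conditional on quitting and follows almost directly from matching a 12-month cut-off to a 12-month interval. That is fair. The Protocol gives no smoking prevalence or quit rate, so the number of affected records is unknown and could be small. Nor does the Protocol name smoking in its objectives, in the follow-up list under Enrolment or under Registry Data Points, and each project is to bring its own analysis plan. The confounding argument is thus a general one. But a project's analysis plan cannot restore a date that was never collected.

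A reader might infer more than the documents support:

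- **That the item misses nearly every change in smoking.** It still records starting, relapse and updated pack-years. Only recent cessation falls in the gap.
- **That cessation is always recorded one visit late.** This does not hold where a site ticks ex-smoker against the rule, and the Protocol does not show which course sites take.
- **That the data can never be corrected.** The bracketing above shows that they sometimes can. The supportable statement is that they cannot be reliably corrected.

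**Conclusion.** The smoking item is not exhaustive, and its cut-off coincides with the visit interval. About 97% of patients who stop between two on-schedule visits have no matching box at the next visit, with a range of 86% to 100% across the permitted intervals and about 50% after one missed visit. These figures assume uniform quit timing and no relapse. Patients who quit in the year before baseline are in the same position.

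The result is a value that is misclassified, inconsistent between sites or missing, usually for one annual record. The impact is modest, because smoking is a covariate, no stated endpoint or figure is contradicted, and the number of patients affected cannot be computed from the Protocol. The item should still be corrected, because enrolment is open-ended and the missing information cannot be dependably recovered afterwards.

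**What to change.** Replace the three boxes with four: never smoker; current smoker; ex-smoker, quit 12 months ago or less; ex-smoker, quit more than 12 months ago. Add month and year of quitting for all ex-smokers. Keep the more-than-12-months status as a derived variable for projects that want it. The form already asks for a date or year for bronchial thermoplasty and start dates for biologics, so a date field of this kind is not new to it.

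The cost is one answer box and one date field, but the change must be made in each country's separate database and carried into the merged file and the OMOP mapping. It may also count as a change to study procedures under Modification of the protocol, which would need a formal amendment and ethics approval according to each country's rules. Records made under the three-box coding need a flag, because their current and ex-smoker values may include recent quitters.

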## Study design

At the baseline study visit, patients will sign an informed consent form, and clinical data from the patient's medical files that are listed in appendix 1 will be collected and entered in the eCRF. Patients will also be asked to complete 6 questionnaires related to asthma.

At each annual follow up study visit, identical data to the ones at the baseline visit will be collected.

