    - salmeterol \_\_\_\_\_ µg/day and Fluticasone propionate\_\_\_\_\_ µg/day
  - beclomethasone / formoterol
    - beclomethasone \_\_\_\_\_ µg/day and formoterol \_\_\_\_\_ µg/day
  - fluticasone / formoterol
    - fluticasone \_\_\_\_\_ µg/day and formoterol \_\_\_\_\_ µg/day
  - fluticasone furoate/ vilanterol[SEP]
    - fluticasone fuorate \_\_\_\_\_ µg/day and vilanterol \_\_\_\_\_ µg/day
- ☐ Fixed LABA/LAMA combination inhaler
  - indacaterol / glycopyrronium
    - indacaterol \_\_\_\_\_ µg/day and glycopyrronium\_\_\_\_\_ µg/day
- ☐ montelukast
- ☐ theophylline
- ☐ Maintenance oral corticosteroids
  - predniso(lo)ne[SEP]\_\_\_\_\_ mg/day
  - dexamethasone \_\_\_\_\_ mg/day
  - betamethasone \_\_\_\_\_ mg/Day
  - hydrocortisone \_\_\_\_\_ mg/Day
  - triamcinolone (injections) \_\_\_\_\_ mg/month

Is patient currently tapering his/her oral/systemic corticosteroid dose?

- ☐ Yes
- ☐ No

Is the patient currently being treated with biologic therapy?

- ☐ Yes, omalizumab

Start date: dd/mm/yyyy

Dose per injection visit\_\_\_\_\_ mg

Frequency of dosing\_\_\_\_\_ weeks

Has omalizumab dose or interval been changed in last 12 months:

- ☐ Yes, because of adverse effects
- ☐ Yes, because of insufficient response
- ☐ Yes, because of (very) good response
- ☐ No

- ☐ Yes, mepolizumab

Start date: dd/mm/yyyy

Dose per injection/visit\_\_\_\_\_ mg

Frequency of dosing\_\_\_\_\_ weeks

Has mepolizumab dose or interval been changed in last 12 months:

- ☐ Yes, because of adverse effects
- ☐ Yes, because of insufficient response
- ☐ Yes, because of (very) good response
- ☐ No

- ☐ Yes, reslizumab

Start date: dd/mm/yyyy

Dose per infusion/visit\_\_\_\_\_ mg

Frequency of dosing\_\_\_\_\_ weeks

Has reslizumab dose or interval been changed in last 12 months:

- ☐ Yes, because of adverse effects
- ☐ Yes, because of insufficient response
- ☐ Yes, because of (very) good response

☐ Yes, dupilumab

Start date: dd/mm/yyyy

Dose per injection/visit\_\_\_\_\_ mg

Frequency of dosing\_\_\_\_\_ weeks

Has dupilumab dose or interval been changed in last 12 months:

- ☐ Yes, because of adverse effects
- ☐ Yes, because of insufficient response
- ☐ Yes, because of (very) good response
- ☐ No

☐ Yes, benralizumab

Start date: dd/mm/yyyy

Dose per injection/visit\_\_\_\_\_ mg

Frequency of dosing\_\_\_\_\_ weeks

Has benralizumab dose or interval been changed in last 12 months:

- ☐ Yes, because of adverse effects
- ☐ Yes, because of insufficient response

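### On the printed CRF, new ICU admissions and intubations during follow-up can be seen only by comparing successive undated lifetime totals, so they are poorly dated and exposed to miscounts

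*Protocol*

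**What the plan says.** In Appendix 1, the page headed "To be completed once every year by case-manager" asks "Has patient ever been admitted to ICU for asthma", answered Yes or No, and then "If yes, total number of ICU admissions". It goes on to ask "Has patient ever been intubated due to asthma", again Yes or No, and "If yes, total number of intubations". No date, recall period or Unknown box is printed for either pair.

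Section 1, Study design, states: "At each annual follow up study visit, identical data to the ones at the baseline visit will be collected". The lifetime questions are therefore repeated unchanged each year.

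Other items in the same appendix are built differently. The item "Has the patient ever attended rehabilitation" has a number of times, the years since the last time, and Unknown. The bronchial thermoplasty item has a date or year, and Unknown. The biologic items have a start date and a defined window, for example "Has omalizumab dose or interval been changed in last 12 months".

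Under Registry Data Points, ICU admissions come from clinic records and patient interview. The primary objective includes the burden of severe asthma during follow-up and patients' responses to treatment. Natural history is a secondary objective.

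**The concern.** A lifetime total is a sensible baseline question. Asked again each year, it gives new events only indirectly, as the difference between two forms or as a first Yes. Three things follow.

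- **Timing.** The event has no date of its own, so it cannot always be related to the start of a treatment or to a calendar year.
- **Recording error.** If a past admission is found late, or a total is entered differently in two years, the difference looks like a new event or becomes negative.
- **Unknown history.** A patient whose past is unclear has no code, unlike for the neighbouring items. If No is entered and later corrected, a false first event appears.

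At stake is the quality of two of the gravest asthma outcomes for any later project on burden, natural history or treatment response. The registry is open-ended, so each further year adds undated events that may be hard to recover.

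**Working it through.** **1. Is there another source of dated events?** The protocol names three candidates.

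- The health care utilization questionnaire is kept on the CRF only as a mean score. Registry Data Points lists it among the additional questionnaires.
- Adverse Event Reporting sends adverse events to the eCRF, but the printed CRF has no general adverse-event form.
- Hospital admissions are named under Registry Data Points, but the printed CRF has no such item.

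None of them shows a dated ICU or intubation field. The Enrolment section gives a shorter list for yearly appointments that does not name ICU events. If that list governs, follow-up is no better served.

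**2. What timing can be recovered?** Each annual page carries an examination date, and each current biologic has a start date. A rise in the total is thus bracketed by two examination dates, about one year apart. If the biologic started before or after that interval, the order is known; if it started inside it, the order is lost. Under Early Withdrawal of Subjects, a missed visit stays in the data as missing. The bracket is then about two years or more, and the event cannot be assigned to a year. This holds even if every total is correct.

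**3. How much could miscounts matter?** The protocol states no ICU rate and no error rate, so there is no figure to reproduce, and every input here is an assumption. Let q be the share of patients with any past ICU admission, λ the probability of one true new admission per year, and e the probability that a yearly total is wrong by one (half up, half down), independently each year and only in patients with a history.

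Probability that error alone raises the difference: f = e(1 − e) + e²/4 = e − 0.75e².

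False share of apparent new events = q(1 − λ)f / [q(1 − λ)f + λ(1 − qf)].

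Example with q = 0.20, λ = 0.01, e = 0.05: f = 0.05 − 0.001875 = 0.048125. The false part is 0.20 × 0.99 × 0.048125 = 0.00953 and the true part is 0.01 × (1 − 0.009625) = 0.00990. The share is 0.00953/0.01943 = 49%.

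| q | λ per year | e = 1% | e = 5% | e = 10% |
|---|---|---|---|---|
| 10% | 2% | 5% | 19% | 31% |
| 20% | 1% | 16% | 49% | 65% |
| 20% | 5% | 4% | 16% | 26% |
| 30% | 0.5% | 37% | 74% | 85% |

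Over q = 10–30%, λ = 0.5–5% and e = 1–20%, the share runs from 2% to 91%.

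**4. Does the error model matter?** A simulation with assumed values of 0.5 for the mean lifetime count and 0.02 true new admissions per patient-year gives these shares of apparent increases that are real:

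| Error model | e = 2% | e = 5% |
|---|---|---|
| Any patient, redrawn each year | 59% | 36% |
| Only patients with an ICU history, redrawn each year | 72% | 51% |
| Any patient, 80% carry the same error forward | 88% | 74% |
| Only patients with a history, 80% carried forward | 93% | 84% |

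Negative differences occur in about 3.3% of patient-years in the worst of these cells and about 0.15% in the best. The mean difference stays at 0.0196 to 0.0201 against the true 0.02. Symmetric error therefore adds noise and misclassifies individual events, but hardly biases the average rate.

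**The case against.** A reader might infer that events derived in this way are mostly recording error. The documents do not support that. The error share depends on rates that the protocol does not give, and plausible inputs put it anywhere from small to a majority. An error in a lifetime count taken from the same clinic records may well repeat from year to year and cancel on subtraction. The protocol also provides range checks, source verification on randomly selected records with complete checking if errors are common (Data Quality), and continuous plausibility review (Monitoring research progress).

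Two further stronger readings also fail. It is too much to say that an event can never be ordered against a biologic, because the dated examinations often settle the order. Nor is unknown history inevitably confused with No: Monitoring research progress says that missing data are marked, so a blank is distinguishable.

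Finally, no ICU endpoint is defined at registry level, and the Sample Size Determination and Statistical Analysis Plan sections leave endpoints and analysis to each project. How projects should estimate rates is therefore not part of this point. What the objection does not remove is the form itself: no checking procedure or later analysis plan can supply a date that the form never requested.

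**Conclusion.** The point holds as a weakness of the data collection form, and it should be corrected. On the printed CRF, new ICU admissions and intubations must be derived from a rise in successive undated lifetime totals or from a No-to-Yes change.

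The timing loss follows from the form alone and needs no assumed rate. It arises when a biologic starts between the two visits, or when a visit is missed. The extent of false or negative events cannot be determined from the protocol. The 2% to 91% range rests entirely on assumed event, history and error rates, and shows only that the problem may be negligible or serious. The missing Unknown option is a smaller coding inconsistency. The conclusion is limited to the CRF as printed; a dated field elsewhere in the eCRF would weaken it, but none is shown.

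**What to change.** Keep the lifetime ICU and intubation questions at baseline and add an Unknown option. On the annual follow-up page, replace them with: the number of ICU admissions for asthma and the number of intubations for asthma since the last completed registry visit, the date of each, and an Unknown option. Anchoring on the last completed visit covers the gap after a missed one. Align the Study design statement that identical data are collected at each visit with this change.

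The cost is a few extra eCRF fields, filled from the same clinic records and interview. If the change is judged to affect study procedures, the Modification of the protocol section calls for a formal amendment and ethics approval under each country's rules.

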## Study objectives

- To collect retrospective and prospective data on the phenotypical characteristics of patients with severe asthma, treatment strategies and patient responses to treatment, burden of severe asthma across Europe at baseline and during follow-up.
- To obtain natural history data on a wide spectrum of severe asthma patients
- To expedite identification and recruitment of participants for clinical trials
- To plan for future research studies (observational and interventional trials aimed at better symptom control and improving quality of life).

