## Objectives

### *Primary Objective*

SHARP CENTRAL Registry is the central registry of ERS SHARP CRC and primarily designed to collect prospective data on the phenotypical characteristics of patients with severe asthma, treatment strategies and patient responses to treatment, burden of severe asthma across Europe at baseline and during follow-up.

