## Participant Selection

### *Inclusion Criteria*

SHARP CENTRAL Registry concerns adult patients ( $\geq 18$  years) with severe asthma in the Europe. Severe asthma is defined according to international ERS/ATS guidelines (16). Briefly, this includes all adult asthma patients with uncontrolled symptoms for at least 6 months despite treatment with medium/high doses of inhaled corticosteroids, with or without oral corticosteroids, in combination with at least one other controller medication (e.g. long acting beta-2-agonists, theophylline), and having been checked for adherence to the medications, inhalation technique and co-morbid factors. These patients qualify for additional treatments for severe asthma, such as biologics. Some patients will already be using these therapies. Patients must be capable of giving informed consent and be able to travel to office/hospital for study visits.

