### Is the patient currently participating in a (randomized) trial in which he/she receives study medication for asthma?

- ☐ Yes  
☐ No

Date of randomization (dd-mm-yyyy):

Year/month of birth (yyyy/mm):

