- ☐ Yes, because of (very) good response

☐ No, patient is currently not treated with biologics

Does the patient currently use any of the following (non-pulmonary) medications?

- ☐ Nasal corticosteroids[L][SEP]
- ☐ Antihistamines[L][SEP]
- ☐ Bisphosphonates[L][SEP]
- ☐ Calcium suppletion ( $\pm$  vit D)[L][SEP]
- ☐ Proton pump inhibitors[L][SEP]
- ☐ vit K antagonists[L][SEP]
- ☐ NSAIDs[L][SEP]
- ☐ Other

-----  
-----  
-----

[L][SEP]

Has the patient received one of the following asthma add-on treatments  
IN THE PAST?

☐ omalizumab

If Yes, date of last administration (dd/mm/yyyy)

If yes, reason for stopping?

☐ insufficient reduction of systemic steroid dose[L]SEP

☐ Adverse effects[L]SEP

☐ Insufficient improvement of symptoms or exacerbations[L]SEP

☐ Insufficient improvement of lung function

☐ mepolizumab

If Yes, date of last administration (dd/mm/yyyy)

If yes, reason for stopping?

☐ insufficient reduction of systemic steroid dose[L]SEP

☐ Adverse effects[L]SEP

☐ Insufficient improvement of symptoms or exacerbations[L]SEP

☐ Insufficient improvement of lung function

[L]SEP

☐ reslizumab

If Yes, date of last administration (dd/mm/yyyy)

If yes, reason for stopping?

☐ insufficient reduction of systemic steroid dose[L]SEP

☐ Adverse effects[L]SEP

☐ Insufficient improvement of symptoms or exacerbations[L]SEP

☐ Insufficient improvement of lung function

[L]SEP

☐ benralizumab

If Yes, date of last administration (dd/mm/yyyy)

If yes, reason for stopping?

☐ insufficient reduction of systemic steroid dose[L]SEP

☐ Adverse effects[L]SEP

☐ Insufficient improvement of symptoms or exacerbations[L]SEP

☐ Insufficient improvement of lung function

[L]SEP

☐ dupilumab

If Yes, date of last administration (dd/mm/yyyy)

If yes, reason for stopping?

☐ insufficient reduction of systemic steroid dose[L]SEP

☐ Adverse effects[L]SEP

☐ Insufficient improvement of symptoms or exacerbations[L]SEP

- ☐ Insufficient improvement of lung function

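### For biologics started before registry entry, the CRF asks for no pre-start values and, for past courses, no start date, so change from a pre-treatment baseline is generally not estimable.

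*Protocol*

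**What the plan says.** The Study objectives in the protocol summary are "To collect retrospective and prospective data on the phenotypical characteristics of patients with severe asthma, treatment strategies and patient responses to treatment". The detailed Primary Objective is narrower on timing: the registry is "primarily designed to collect prospective data on the phenotypical characteristics of patients with severe asthma". It still lists response to treatment, and the text under Secondary Objectives adds the search for clinical predictors of response. The detailed Inclusion Criteria state that "Some patients will already be using these therapies".

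Under Study design, the data taken from the medical file are those listed in Appendix 1, and annual visits repeat the baseline items. In Appendix 1:

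- Spirometry carries the instruction "If done multiple times, please report most current result". FeNO, diffusion capacity, body plethysmography, blood counts, total IgE and sputum each ask for the date of the latest result.
- Blood counts have one further item: "If yes, what was the highest eosinophil count ever measured". It has no date field.
- Questionnaire scores are entered once a year, and the maintenance oral steroid dose is the current one.
- Each current biologic has a start date and an item on dose or interval change in the past year, with the reason.
- Each past biologic has "If Yes, date of last administration (dd/mm/yyyy") and a reason for stopping. The four reasons are insufficient steroid reduction, adverse effects, insufficient improvement of symptoms or exacerbations, and insufficient improvement of lung function.

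**The concern.** Response to a biologic is usually measured as change from the state just before the first dose. For a patient already on treatment at entry, the registry's first record is usually an on-treatment record. If it is used as the baseline, improvement that has already happened is invisible. Markers that the drug itself lowers, such as blood eosinophils, may then misrepresent the patient's phenotype. Predictors of response suffer in the same way.

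For courses already finished, a missing start date means that duration of exposure is unknown. The closed list of stop reasons also means that a stop for access or patient choice must be coded as a failure or an adverse effect, or left blank. This matters because the stop reason is one of the few response items these patients have.

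**Working it through.** The plan states no sample size, power or effect size on this point, so there is no figure to reproduce. The check is a comparison of fields: for each measure of response, does Appendix 1 request a value from before the biologic was started?

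1. **Lung function, FeNO, IgE, sputum, blood counts.** The latest dated result only. For a prevalent user this precedes the start date only by chance, if the test has not been repeated since. Such a value serves as a baseline only if a later on-treatment test is then recorded.
2. **ACQ and the other questionnaires.** Annual, from entry onward. No pre-start score.
3. **Maintenance oral steroids.** Current dose only. No pre-start dose.
4. **Exacerbations.** No pre-start count is requested. I found no separate exacerbation-count field in the form at all; the health care utilization questionnaire may hold related information, but the form takes only a mean score from it.
5. **Highest eosinophil count.** It may come from before the start, but without a date or steroid/biologic status it cannot be placed. As a maximum it also tends to rise with the number of tests done.
6. **Start dates.** Present for current biologics. Absent for a biologic already stopped at entry, or begun and stopped between two annual visits. A biologic once recorded as current and stopped later does have a start date, from the earlier annual record.
7. **Categorical response.** Present, as stop reason and as reason for dose or interval change.

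**Can it be repaired later?** Under Statistical Analysis Plan, each project writes its own plan. Under Administrative responsibilities, researchers receive a recoded excerpt. Under Data Management and Quality Plan, the data are anonymised before merging, and identifying information is opened only for medical urgency. The protocol describes no route by which a project could return to the charts for a missing baseline.

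**Illustration of size.** Let p be the share of N entrants already on a biologic. About p × N patients lack a requested baseline for it. The protocol does not give p; I assume 20%, 40% and 60%.

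- If prevalent users show no further change and are pooled with new starters, the pooled change is (1 − p) × true + p × 0, so the fraction retained is 1 − p: 80%, 60% and 40%.
- If prevalent users are excluded instead, the standard error grows by 1/√(1 − p): 1/√0.8 = 1.12, 1/√0.6 = 1.29 and 1/√0.4 = 1.58, that is 12%, 29% and 58%.

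The protocol plans neither analysis.

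**The case against.** Four arguments carry weight.

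- **The registry is mainly prospective.** The detailed Primary Objective says so; retrospective data appear only in the summary (Type of Study and Study objectives). A prospective registry that does not reconstruct earlier baselines is limited but does not plainly fail that objective. This stands, and it lowers the severity. It does not remove the mismatch with the summary objective.
- **The bias is avoidable.** Current biologics have start dates and tests have result dates, so an analyst can identify prevalent users and restrict to new starters, whose earlier annual records supply a baseline. This stands. The cost is the loss of the prevalent users.
- **Response is not wholly unrecorded.** A reader might infer that only the latest test value and only a last-dose date are kept, and that response in these patients cannot be assessed at all. The form does not support that: it also takes the highest eosinophil count, the stop reason and the reason for dose or interval change. What is lost is quantitative change from a pre-treatment baseline.
- **Historical values are imperfect.** Patients still on a biologic at entry are selected for having continued it, and old ACQ or FeNO values will be missing for reasons tied to local care. Both points stand. They limit what the added fields can deliver, but the fields still add information that the form does not now request.

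**Conclusion.** The point holds in a limited form. For biologics started before entry, Appendix 1 requests no pre-start lung function, FeNO, ACQ, maintenance steroid dose or exacerbation count, and the one historical marker cannot be dated. Quantitative change from a pre-treatment baseline is therefore generally not estimable, with the chance exception of a latest test that precedes the start date. Finished courses without a start date have unknown duration, and stops for reasons outside the four listed are miscoded or left blank. Project-level analysis plans cannot recover values that were never collected.

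The size in this registry is unknown. A reader might take the 80/60/40% retention or the 12–58% wider standard errors as properties of the plan. They are not: they rest on assumed shares of prevalent users, and the first set also on naive pooling with no further change. This is a worthwhile and inexpensive improvement to the form, not a defect that invalidates the registry. Patients who start after entry have earlier annual records to serve as baseline.

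**What to change.** Amend Appendix 1 as follows:

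1. For each current or past biologic, record the last available value before the first dose, with its date, for a short core set: FEV1, blood eosinophils, FeNO, ACQ, maintenance steroid dose, and exacerbations in the preceding 12 months. Enter it once, and only where the file holds it. The exacerbation count needs a matching annual item if change is to be derived.
2. Add a start date for each past biologic.
3. Add 'other, specify' to the stop reasons.
4. Add a date and steroid/biologic status at the time to the highest eosinophil count.

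The cost is a CRF amendment and some extra baseline entry for patients with biologic exposure, from the file review that sites already do. Missing historical values will not be random, and survivor bias among patients still on treatment at entry remains. The data should therefore keep new starters separable from prevalent users, so that new-starter analyses can be run alone. Patients enrolled before the change will lack these fields unless their files are revisited, so an early amendment is worth more than a late one.
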